**Expected Adverse Events**

An expected adverse event is an AE for which the nature, severity, or degree of incidence is known and identified in the study protocol. Expected adverse events associated with this study include:

**1) Breach of confidentiality** associated with data collection and necessary reporting of increased participant risk (suicide risk, homicide/retaliation risk, or risk based on increased substance use) to appropriate authorities or health personnel.

There is a minor potential risk to the confidentiality of survey data and audio-recorded (via UTHealth Teams) sessions. Precautions to protect subject confidentiality will be maintained through the use of study identification numbers and data stored in password-protected files on UTHealth password protected servers. All personnel assisting in data collection have been trained to perform required tasks safely, effectively, and efficiently and maintain patient confidentiality. Only the principal investigator, co-investigators, and necessary research personnel will have access to this data. Study staff will have procedures in place to ensure data confidentiality.
 **2) Homicidal ideation/retaliation risk** as indicated by verbal report of thoughts of hurting others.

We conduct an assessment of retaliation risk given that the initial injury occurred during a violent altercation. Further, homicidal or retaliatory thoughts may also be provided by the participant during an interaction with study team members. The protocol for handling homicidal ideation or retaliation risk will be similar to that for suicidal ideation. Specifically, if the participant articulates thoughts of hurting others, the study team member will ask the participant to elaborate on his/her thoughts/behaviors (e.g., is there an identified victim, does the participant have a plan). The level of action necessary will be based on the participant’s responses and whether the study team member perceives that the patient or someone else is in immediate danger. If a participant espouses any retaliatory ideation during subsequent interactions with staff, a homicidal ideation screener will be provided to the participant by a case manager to assess risk. Study personnel will follow established safety protocols and contact local licensed clinical staff when appropriate.

Our team has extensive experience studying high-risk patients and have concrete plans to manage potential risks, including suicide risk, retaliatory risk and/or disclosure of child abuse. Briefly, all participants will be informed during consent that we will need to inform a mental health provider if they are determined to be at significant risk and/or if they disclose information regarding risks during sessions or in the course of study procedures. Measures at baseline/follow-up will assess suicidality and retaliation risk; they will flag if endorsed, prompting formal risk assessment. A determination of high-risk status will be made through review of these measures, the formal risk assessment criteria, and discussions when appropriate with a licensed clinician (e.g., [name]). Whenever possible, if a participant is determined to be at high acute risk, we will engage them in the process of disclosing this to a provider (at baseline enrollment) and/or aid in contacting them with appropriate resources (during the intervention or at follow-ups). We will only break confidentiality if it is determined that it is necessary to manage the acute risk (e.g., homicidal/retaliatory threats) and the participant is unwilling to engage in this process.

Drs. [name] and [name] will provide supervision to research staff who have direct contact with patients, including crisis procedures for suicide and homicide risk and clinical assessment and referral procedures for participants who meet threshold criteria for suicide or homicide. Supervision will focus on procedures for managing issues that could arise given the patient population, including potential crisis situations and/or adverse events around violence and/or substance use. Procedures will include a review of the study protocol regarding the limits of confidentiality, how to liaison with study site staff (i.e., psychiatry, crisis management) to arrange for an assessment, circumstances in which it may be necessary to notify parents/authorities regarding intent to harm self or others, and the development of safety plans and resources. The crisis procedures also will include immediately notifying Drs. [name] and [name] for consultation and conference call discussions on any risk assessments that meet more than minimal risk. Other investigators will be involved as necessary, and a 24/7 study staff member and investigator will be on call to manage crisis calls by participants at all times.

**3) Hospitalization or Emergency Department/Urgent Care visits** as a result of mental health (e.g., suicide attempts), substance use (e.g. acute intoxication, acute withdrawal), or violent injury (e.g., gunshot wound, assault injury).
 **4) Severe Emotional Distress**a. patient verbal report of a significant increase in psychiatric symptoms;

b. patients reporting significant distress due to the content of the self-report measures;

c. patients reporting significant distress due to the content of the case management sessions.

d. patients reporting significant distress due to talking about or reliving the experiences of the traumatic event.

Participants will be informed during the consent process and again at the start of each interview that they are free to “skip” any interview question or prompt that makes them uncomfortable and free to end their participation in the interview at any time. They will also be provided with information to contact the study MPIs and UTHealth IRB to discuss any concerns they might have about the study. [name] and [name] and several Co-Is ([name], [name]) have experience conducting these types of interviews with individuals who have a history of trauma. All study staff members who conduct in-depth interviews and interact with the study population will be trained beforehand in trauma-informed care to be sensitive to signs of participant discomfort or distress. Participants will be provided with information about available mental health resources throughout the duration of the study. Available mental health resources and mental health resources at Memorial Hermann Hospital will be made available to all participants.

In each case, the case manager and study staff will consult with the PIs to determine whether the participant’s distress was significant enough to warrant reporting as an AE.
 **5) Suicidal ideation**

a. self-report of significant suicidal ideations and behaviors on pertinent study surveys

b. endorsement of recent suicidal thoughts, plans, or actions during the assessment or intervention sessions

c. endorsement of thoughts of suicide or suicidal behaviors during the assessment or intervention sessions.

In each case, the case manager and study staff will follow the suicide risk assessment protocol and consult with the PIs to determine whether the participant’s distress was significant enough to warrant reporting as an AE.

**6) Psychological discomfort** as a result of being asked personal questions, particularly during the assessments and sessions. While we do not anticipate significant psychological distress during study, we will monitor reported distress during interviews so that participants can receive additional assessment and referrals as needed. If signs of discomfort or distress are detected and reported by interviewers to the study team, we will notify the participant. All participants will also be provided with information about available mental health resources and mental health resources at Memorial Hermann Hospital will be made available to all participants.

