The randomization scheme will be generated and then uploaded into REDCap under the randomization module to ensure equal allocation to the treatment and control arms. Specifically, the randomization module will utilize a blocked randomization procedure with varying block sizes to ensure that the number of participants in each group remains balanced throughout the enrollment process. The REDCap system will automatically assign participants to either the treatment or control condition based on this scheme, ensuring allocation concealment. The intervention will be administered at the individual level. This study will require voluntary, informed written/e-consent from the adult patient and from the parent(s)/LAR and an assent for the minor patient. (ages 16 and 17). Individuals who do not provide voluntary informed written consent/e-consent will not be included in either the treatment or comparison group and will not be included in the study. Once an individual participant eligible for enrollment is selected, a designated case manager can log in to the secured REDCap system and obtain a computer-generated randomization assignment in a timely manner. Authorized, unblinded individuals who need this information to provide the appropriate intervention successfully will receive an automated notification. Due to the nature of the proposed intervention, case managers will be unblinded regarding the group assignment but will be blinded to the outcome data. Participants will be partially blinded in that they will know some information about the intervention but will not be exposed to the details of the intervention or the intervention manual. The study personnel who collect or evaluate outcome data will be blinded to the intervention. Data will be collected and stored on a readily accessible dashboard hosted through REDcap and maintained by the School of Public Health throughout the project.

**Intervention Implementation.** The intervention will be implemented during the UH3 phase using a fully powered RCT with eligible participants assigned to the Houston-HVIP program or the standard of care comparison group. Ultimately, coalition members will provide input on the intervention implementation and delivery through surveys and focus groups to provide guidance on the feasibility and acceptability of the program components.

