**Recording and Reporting Adverse Events**

At each evaluation, study staff (case manager, program manager, and/or graduate research assistant) will determine whether any adverse events (AEs) have occurred. All AEs that occur between enrollment and subject exit will be documented in a timely manner. As the PIs, Drs. [name] and [name] will have the ultimate responsibility for monitoring the overall safety of the participants in the study, determining whether an event is considered an adverse event (AE) or serious adverse event (SAE), and reporting events as needed to the appropriate committees and agencies. Study personnel will be expected to notify the lead PI, Project Manager, or other designated coordinating center personnel of serious adverse events, noncompliance, or other study related problems as soon as they are identified. In all instances where participant safety is a concern, the participant will be evaluated and connected with the appropriate level of treatment services necessary. Senior clinicians (Drs. [name] and [name]) are always on call for consultation if a participant seems distressed or needs special attention for medical or mental health-related issues. All participants will be instructed on how to obtain emergency care, should that be required.

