**Data Safety Monitoring Board:**

A Data Safety and Monitoring Board (DSMB) will be convened for this study.

The Co-Principal Investigators (PI) will be responsible for ensuring participants’ safety on a daily basis. In addition, the study will impanel a Data and Safety Monitoring Board (DSMB) to act in an advisory capacity to the PI and to evaluate the progress of the study, including periodic assessments of data quality and timeliness, participant recruitment, accrual and retention, participant risk versus benefit, performance of trial sites, and other factors that can affect study outcome.  The DSMB will make recommendations to NINR’s Director concerning the continuation, modification, or conclusion of the trial.

Roles and Responsibilities: The DSMB will review study protocols and provide oversight of recruitment progress, data quality and completeness, efficacy monitoring, and participant safety pertaining to the study. The research team will be responsible for providing study protocols, data, and adverse event reports to the DSMB. All recruitment and data collection will be conducted in Houston, Texas.

DSMB Membership and Affiliations: The DSMB will be comprised of 5 individuals external to the grant to provide safety monitoring and oversight. All members of the DSMB will be external to the grant.

Frequency and Types of Meetings:

The DSMB will meet annually (at a minimum) via teleconference to review the study progress, data quality, and participants' safety.  During these meetings, the PIs and Co-Is will provide the DSMB with an update on study recruitment and enrollment, the progress of participants within the study, and the presence of all AE/SAE, including classifications based on severity, expectedness, and relatedness to study procedures.  The DSMB will then have private discussions and provide recommendations as appropriate.

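### Reporting of suicidality as an adverse event turns on the participant's distress, which is not the event that item 5 lists, so some events may not reach the DSMB

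*Protocol*

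**What the plan says.** Under Expected Adverse Events, the protocol opens a list with the words "Expected adverse events associated with this study include". Item 5 of that list is suicidal ideation, and it has three triggers:

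- Trigger a comes from the questionnaires: "self-report of significant suicidal ideations and behaviors on pertinent study surveys".
- Trigger b comes from contact with staff: "endorsement of recent suicidal thoughts, plans, or actions during the assessment or intervention sessions".
- Trigger c covers suicidal thoughts or behaviors voiced in those same sessions.

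For all three, the protocol for assessing suicide risk is applied, and the case manager and study staff also "consult with the PIs to determine whether the participant’s distress was significant enough to warrant reporting as an AE".

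Three other sections bear on what happens next.

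- Recording and Reporting Adverse Events states that "All AEs that occur between enrollment and subject exit will be documented in a timely manner". It also gives the PIs final responsibility for "determining whether an event is considered an adverse event (AE) or serious adverse event (SAE)".
- Data Safety Monitoring Board, on meetings, says that the board is updated on "the presence of all AE/SAE, including classifications based on severity, expectedness, and relatedness to study procedures".
- Data and Safety Monitoring says that the research team supplies the board's data and adverse event reports. It also says that the board evaluates all events, including their expectedness, relationship and severity.

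**The concern.** The reporting test in item 5 measures something other than the event. None of the three triggers mentions distress. A person can report a suicide plan without visible distress, and another can be very distressed with little ideation. A test on distress therefore sorts suicidality events by a different construct before they are classified.

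What is at stake is safety oversight of a risk that the protocol itself names. If an event is judged not distressing enough, it is not reported as an AE, and the DSMB has no stated way to learn of it. The board's own assessment of expectedness, relationship and severity then covers only the events that passed this test.

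**Working it through.** No calculation decides this point. The check is to read the sections against each other.

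**1. Where the test comes from.** Item 4, Severe Emotional Distress, closes with the same consultation about whether distress was great enough to report. There the test fits, because distress is the event. Item 5 repeats it for a different event.

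**2. Whether distress appears elsewhere as a criterion for suicidality.**

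| Place in the protocol | Criterion used |
| --- | --- |
| Item 5, triggers a to c | Suicidal thoughts, plans, actions, behaviors |
| Adverse Events (definition) | Undesirable or unintended occurrence attributable to the intervention |
| Data Safety Monitoring Board | Severity, expectedness, relatedness |
| Item 5, closing sentence | Degree of distress |

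Only the closing sentence uses distress.

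**3. A case followed through the rules.** A participant calmly endorses a suicide plan in a session three months after enrolment.

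- Trigger b is met.
- The risk assessment is carried out, as item 5 requires.
- The PIs are consulted and judge distress not significant enough, so the event is not reported as an AE.
- The rule to document AEs covers AEs, so it is satisfied.
- The meeting update covers AEs and SAEs, so it is satisfied too.
- The event need not appear in anything that the protocol says the DSMB receives about adverse events.

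Every rule has been followed, yet the general statement that the board evaluates all events is not met for this one.

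**4. How far the gap reaches.** Item 3 lists hospital, emergency or urgent care visits for mental health reasons, with suicide attempts as an example, and has no distress test. Serious Adverse Events sets its own criteria, again without distress. The gap is what remains: ideation, plans and behaviors that lead to no such visit and meet no SAE criterion.

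**5. Size.** The protocol gives no rate of suicidal ideation and no expected share of triggers that would fail the test. The only available count is of planned surveys: 274 participants × 4 follow-up surveys (3, 6, 9 and 12 months) = 1,096. With 274 baseline surveys the total is 1,370. These are ceilings on screens under full follow-up, and the sample size section allows up to 35% attrition. They are not event counts, and no number of unreported events can be derived from them.

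**The case against.** The strongest reply is that deciding AE status is the PIs' job. The protocol says so in the same section that requires all AEs to be documented. A reader might infer that item 5 contradicts the rules on documenting AEs and on informing the DSMB. It does not: both rules apply to events classed as AEs, and item 5 is one place where that classing happens. This part of the reply stands. It does not rescue the criterion.

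A reader might also infer that every trigger should automatically be an AE. The protocol defines an AE as attributable to the intervention. Suicidality is assessed at baseline, and the baseline survey is planned before hospital discharge, so a flag there describes status before the case-management programme. Trigger a also contains a judgement, since it asks for significant ideation. Automatic recording would conflict with the definition and with the PIs' role.

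A third tempting reading is that suicide attempts can go unreported or that events are deliberately withheld. Attempts that lead to care and events that meet SAE criteria escape the distress test, and nothing in the text suggests intent. Clinical handling is also outside the test: survey flags prompt a formal risk assessment, and more than minimal risk is escalated to the supervising investigators.

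Finally, "case managers will be unblinded regarding the group assignment", and they take part in the consultation. A reader might blame the test for any difference between arms in session-based counts. The documents do not support that as the main cause. Case-manager contact runs over six months with at least eight contacts in one arm and over two weeks after discharge in the other, so triggers b and c will be detected unequally under any reporting rule.

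One reply remains open. The detailed Data and Safety Monitoring Plan and the suicide risk assessment protocol are mentioned but not shown, and either might give a route to the DSMB. The protocol's own wording would still need to agree with it.

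**Conclusion.** The point holds in a limited form. Item 5 fixes a wrong criterion for reporting suicidality, apparently carried over from item 4. As written, ideation, plans and behaviors short of an item 3 visit or an SAE can meet a listed trigger and yet may not reach the DSMB. The statement that the board evaluates all events gives no route for those screened out earlier, so the two passages need to be reconciled.

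That an event would be missed is an inference from following the rules literally. It assumes that no document outside the protocol supplies the route. No magnitude can be stated. The primary efficacy analysis does not depend on this. The consequence is confined to safety oversight, where the change is cheap and worth making.

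**What to change.** In item 5, replace the distress test with a determination based on the result of the suicide risk assessment and on the protocol's own AE definition. Reconcile the item with the statement in Data and Safety Monitoring that the DSMB evaluates all events.

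Record every post-enrolment trigger a, b or c in a log, with the PIs' classification and the reason for it. Give the DSMB that log and, by arm, the count of follow-up survey flags beside the recorded AEs. Show baseline flags separately as status before the intervention. Leave the clinical response and the PIs' authority over AE status as they are.

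The cost is a short protocol edit and some extra forms and listings. Counts from triggers b and c will still differ by arm because case-manager contact differs. The survey flags, collected on one schedule in both arms, are the measure to compare.

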**Unexpected Problems (UP)**

An unexpected adverse event is an event that is not listed as a risk in the protocol or consent forms, or was not previously documented/observed in our study population. For an event or information to be considered an “unanticipated problem,”' three criteria must be met:

1. It must be **“unanticipated.”** This means the event is not expected in terms of its nature, severity or frequency given the:

o Procedures described in the study documents (e.g. the application, protocol, data and safety monitoring plan, etc.)

o Characteristics of the subject population being studied (the traits, behaviors, symptoms, diseases, life experiences, or other qualities typically found in the persons comprising those eligible to participate in the study). A UP is a problem that was expected by neither the research participants nor the investigators.

1. It must **be “related to the research.”** This means there is a reasonable possibility that the event or information may have been caused by, or is linked in a significant way, to the research. This encompasses all aspects of the research; it is not limited to test agents or procedures.
2. The event or information suggests that the **research places subjects or others at greater risk of harm than was previously known or recognized.** This includes physical, psychological, economic, or social harm:

o **Type 1:** Potential harm - Possibility that previously unsuspected harm may occur (or may occur at a higher than expected rate) even though no one has yet experienced actual harm.

o **Type 2:** Actual harm - Recognized harmful or unfavorable outcome that has actually occurred to a research subject, a set of subjects, another individual being treated in a similar fashion in a relevant non-research setting, or another person connected to the research study.

**Serious Adverse Events**

A Serious Adverse Event (SAE) is any untoward occurrence or effect that:

- Results in death
- Is life threatening
- Requires inpatient unplanned hospitalization or prolongation of existing hospitalization
- Persistent or significant disability/incapacity
- An important medical event that may not result in death, be life threatening, or require hospitalization may be considered an SAE when, based upon appropriate medical judgment, the event may jeopardize the subject and may require medical or surgical intervention to prevent one of the outcomes listed in this definition.

More than one of the criteria above can be applicable to one event.

